### Patients and enrollment

2.3

We will enroll patients hospitalized for stable or unstable angina pectoris in Beijing Anzhen Hospital, The First Affiliated Hospital of Dalian Medical University and Beijing Friendship Hospital from April of 2018 to December of 2021 meeting the selection criteria. All subjects/guardians enrolled in the trial should clearly understand the research requirements and intervention procedures, and each will be required to sign a written informed consent agreement before participating in any type of examination or intervention. All participating research centers should obtain all informed consent forms from patients before the initiation of intervention. Personal information will be kept confidential before, during, and after the trial.

#### Inclusion criteria

2.3.1

To meet inclusion criteria, patients should: be 18 to 80 years old; be diagnosed with single CTO concurrent with MVD detected using coronary angiography (at least one other major vessel should have exhibited no less than 75% stenosis); previously have been diagnosed with myocardial infarction, or suffer from myocardial necrosis in the territory of CTO artery determined by CMR; present with an LVEF above 35% determined using transthoracic echocardiography; present with CTO located in an epicardial coronary artery with a reference diameter of ≥ 2.5 mm; and comply with all the evaluations and follow-up protocols.

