**Methods and results::**

Patients will be prospectively recruited who meet the following criteria:

Patients presenting with no necrosis of myocardial tissue in the territory of the CTO will be excluded. Recruited patients will be randomized into 2 groups: those undergoing PCI of only the non-CTO artery (non-CTO PCI group), and those undergoing PCI of the non-CTO artery concurrently with the CTO artery (CTO-PCI group). The primary outcome will be the change in cardiac function evaluated via CMR at a 12-month of follow-up appointment, which will be compared to a baseline measurement. Secondary outcomes include occurrence of major cardiac events, CMR-assessed myocardial viability in the CTO-supplied territory, and quality of life assessed by Seattle angina questionnaire, Patient Health Questionnaire 9 and Generalized Anxiety Disorder Scale-7 after 12-month follow-up.

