**Conclusion::**

The SOS-moral trial will provide data necessary to determine whether to open concurrent CTOs among MVD patients with CMR-detected necrotic myocardial tissue.

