#### Exclusion criteria

2.3.2

Patients will be excluded if they have suffered from acute myocardial infarction within the previous 3 months; a lesion located in the left main artery (stenosis ≥50%); rheumatic valvular disease; severe arrhythmia; a history of revascularization within the non-CTO artery; multiple vessels with CTO (more than one CTO artery); lesions unsuitable for PCI; severely abnormal hematopoietic systems, such as platelet counts <100 × 10^9^/L or > 700 × 10^9^/L and white blood cell counts < 3 × 10^9^/L; with active bleeding or bleeding tendencies (active ulcers, short-term ischemic stroke, history of hemorrhagic stroke, intracranial space occupying lesions, recent craniocerebral trauma, and other bleeding or bleeding tendency); severe coexisting conditions, including severe renal function dysfunction [Glomerular filtration rate less than 60 ml/min • 1.73 m^2^), severe hepatic dysfunction [glutamic-pyruvic transaminase (ALT) or glutamic-oxal acetic transaminase (ALT) elevated more than three times that of the upper limit of the normal reference], severe heart failure (NYHA classification III–IV), acute infectious diseases and immune disorders; tumors; surgery within 3 months; a life expectancy less than 12 months; pregnancy or planning to become pregnant; history of allergy or adverse reactions to aspirin, clopidogrel, ticagrelor, stains, contrast material, anticoagulant, or stents. Patients will also be excluded if they cannot tolerate dual antiplatelet treatment; are unable to communicate due to cognitive impairment, auditory, or visual impairment; are participating in another trial for medication or an apparatus and in which the main endpoint has not been reached, or plan to participate in a clinical trial within 12 months of the intervention.

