### Sample size calculation

2.7

PASS 15.0 will be utilized to calculate sample size. In the study, 226 individuals are predicted to be recruited in the trial. This sample size was calculated using the optimal efficiency test. The main purpose of this trial is to investigate the effect successfully opening concurrent CTO lesions on cardiac function in patients with MVD. LVEF has been taken into consideration for the calculation of sample size. Previous studies revealed a 6.5% mean difference between the two experimental groups and a 9% standard deviation with respect to LVEF. The optimal boundary value for LVEF was set to 4%.^[21]^ Two-hundred sixteen cases recruited to the study will allow for the use of a 1-tailed test with a significance level (α) set to 0.025, and power (1-β) of 0.90. Ultimately, it is estimated that 240 patients will be randomized, and a 10% loss is expected to occur throughout the 1-year follow-up period.

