Previously, 128 patients were observed using CMR, and among the myocardial regions that corresponded to 149 CTO lesions, only 11.5% presented as transmural myocardial infarction. In fact, 58.6% of the myocardial segments showed no delayed enhancement.^[29]^ Differences in myocardial viability may contribute to the variable prognosis of CTO-PCI. A previous study including 32 CTO patients presenting with significant inducible perfusion deficits found that recanalization was associated with decreased ischemic burden, improved QOL, and reversed remodeling.^[23]^ The effect of CTO-PCI on cardiac function among patients with necrotic myocardial tissue in the territory supplied by the CTO combined with MVD requires further investigation. The present SOS-moral study excludes those patients with complete myocardial survival in the CTO artery territory. This distinction will facilitate the investigation of the effects of actively opening concurrent CTO lesion in MVD patients with necrotic myocardial tissue identified via CMR in the territory supplied by the CTO, aiming to provide reliable evidence for use in clinical practice.

CMR is an appropriate approach for the evaluation myocardial viability and cardiac function. The method is accurate, safe, and provides great spatial resolution as well as sensitivity.^[30]^ CMR has been used to assess myocardial viability throughout the previous decade. According to Cardona et al., CMR accurately detects myocardial viability in patients with reduced LVEF.^[17]^ We previously demonstrated that, using PET as gold standard, CMR has high consistency, sensitivity, and specificity for the detection of myocardial viability compared with PET in CTO patients.^[31]^ Therefore, in the SOS-moral trial, CMR will be used to evaluate both the amount of viable myocardial tissue and level of cardiac functioning.

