## Conclusions

4

SOS-moral will sort myocardial viability before randomization to avoid the effect of viability of myocardial on cardiac function. Hence, the real benefits of CTO-PCI on cardiac function among these patients without 100% survival viable myocardial will be assessed. Furthermore, the present trial strictly recruits patients with MVD and concurrent CTO. SOS-moral will provide evidence for the value of CTO-PCI among these selected patients. Nevertheless, there remain several potential limitations in this study. First, SAQ may be affected by factors other than recanalization of CTO artery during the study period. Second, patients with high risk such as those with left main artery disease stenosis ≥50% and severe arrhythmia are not included. Patients with left main artery disease are not eligible because the PCI procedure needs to be individualized. Because cardiac function might be affected by the severe arrhythmia, those with severe arrhythmia will be excluded. Therefore, the outcomes are unable to include all patients at high risk. Third, in a limited study period, the study may be not powered to detected MACE differences between the two groups. Therefore, further studies including high-risk patients and with longer follow-up periods are needed in the future.

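### The inclusion criterion accepts any previous MI in place of CMR necrosis in the CTO territory, so it admits some patients whom the Abstract and Discussion say are excluded.

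*Protocol article*

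**What the plan says.** Section 2.3.1 (Inclusion criteria) lists among its requirements that patients "previously have been diagnosed with myocardial infarction, or suffer from myocardial necrosis in the territory of CTO artery determined by CMR". Section 2.3.2 has one item on infarction: "Patients will be excluded if they have suffered from acute myocardial infarction within the previous 3 months". It also rules out earlier revascularization of the non-CTO artery. Nothing in that list deals with a CTO territory free of necrosis.

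Elsewhere the article describes a stricter rule:

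- Abstract, Methods and results: "Patients presenting with no necrosis of myocardial tissue in the territory of the CTO will be excluded".
- Abstract, Conclusion: the trial is to inform "whether to open concurrent CTOs among MVD patients with CMR-detected necrotic myocardial tissue".
- Section 3 (Discussion): "The present SOS-moral study excludes those patients with complete myocardial survival in the CTO artery territory".
- Section 4 (Conclusions): "the real benefits of CTO-PCI on cardiac function among these patients without 100% survival viable myocardial will be assessed".

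**The concern.** The case for the trial rests on tissue status. Section 1 attributes part of the disagreement among earlier studies to ignoring it, and sets the aim in patients with multi-vessel disease and necrotic myocardium. If sites enrol by 2.3.1 and 2.3.2, a history of MI is enough, wherever the infarct lay and whatever the baseline scan shows in the CTO territory. Some patients the trial says it leaves out could then be randomized. The primary LVEF result would be an average over a wider group than the one named in the conclusions. Two sites reading different parts of the document could also decide differently on the same patient.

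**Working it through.** The point depends on no figure in the plan. It is settled by setting the eligibility texts side by side.

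**Step 1: test cases**

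| Patient | 2.3.1 and 2.3.2 | Abstract and Discussion |
|---|---|---|
| Necrosis in CTO territory on CMR, with or without prior MI | eligible | eligible |
| No prior MI, CTO territory fully viable | not eligible | excluded |
| MI more than 3 months ago in a non-CTO territory, that artery since revascularized, CTO territory fully viable | not eligible (revascularization exclusion) | excluded |
| MI more than 3 months ago in a non-CTO territory, artery never revascularized, CTO territory fully viable | **eligible** | **excluded** |

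Only the last row conflicts. The same conflict would arise for a recorded MI that the baseline scan does not confirm in the CTO territory, because the first alternative asks for no CMR finding.

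**Step 2: can the share be estimated?** The nearest figure, in the Discussion, is that "58.6% of the myocardial segments showed no delayed enhancement", from 128 patients with 149 CTO lesions. It counts segments. A patient with partial necrosis belongs to the target population and still contributes unenhanced segments. The figure gives no share of patients without necrosis, and still less the share among patients with a prior MI who also pass 2.3.2.

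**Step 3: can the effect on the LVEF difference be signed?** This is an illustration only. The share q of patients entering by history alone, the effect of 4 points in patients with necrosis and the effect e in the others are all assumptions. The 4 is taken because it reproduces the planned size. With a difference of 4, SD 9, one-sided alpha 0.025 and power 0.90, the normal formula gives 2 × 9² × (1.960 + 1.282)² / 4² = 106.4, so 107 per arm. The t-test version gives 107.4, so 108 per arm and 216 in total; 216 / 0.9 = 240. Section 2.7 calls the 4 a boundary value, not an effect in necrotic territory. The value e = 6.5 is the mean difference from earlier studies in section 2.7 and is not specific to viable territory.

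Overall difference = (1 − q) × 4 + q × e:

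| q | e = 0 | e = 6.5 |
|---|---|---|
| 5% | 3.8 | 4.1 |
| 20% | 3.2 | 4.5 |
| 40% | 2.4 | 5.0 |

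The results fall on both sides of 4. If e = 0, power at 108 per arm, Φ(d / (9 × √(2/108)) − 1.960), would go from 0.904 at d = 4 to 0.873 at q = 5% and 0.743 at q = 20%. If e exceeds 4, power would rise. The documents do not say which case applies.

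**The case against.** Four arguments can be made for leaving the text alone.

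- *The territory phrase may qualify both alternatives.* This is grammatically possible, and it would agree with the Abstract and Discussion. The comma before *or* and the separate verb in the second half favour two independent routes. A criterion that can be read both ways still needs rewording.
- *The Abstract sentence may act as an additional exclusion.* Section 2.1 places the viability scan before intervention, and section 4 says viability is sorted before randomization, so the intention is probably the strict rule. But 2.3.2 is a long, detailed list and does not carry it. The Abstract's own list of criteria and Figure 1 could not be read in the available text; neither would remove the conflict with 2.3.1 as worded.
- *The exposed group is narrow.* This stands. Patients without prior MI and with a viable CTO territory still fail 2.3.1, and the revascularization exclusion removes more.
- *Eligibility applies equally to both arms.* This also stands. It is settled before allocation and does not bias the comparison.

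A reader might infer from the 58.6% that a large part of the enrolled patients would lack necrosis, or that the trial readmits the whole group it meant to remove. Neither follows: the figure is per segment, and only patients with a prior MI can enter by this route.

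**Conclusion.** The inconsistency is real. Sections 2.3.1 and 2.3.2 admit patients with a prior MI and no necrosis in the CTO territory, while the Abstract and Discussion exclude them and both sets of conclusions speak for the narrower population. This rests on reading the two halves of the criterion as alternatives, which is the natural reading. Its size is unknown because the documents give no patient-level share.

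It would be tempting to say that the LVEF effect is diluted or the trial underpowered. The documents support neither, since the direction depends on how viable territory responds. What is affected is the population to which the primary result applies, not the validity of the comparison between arms. This is an internal inconsistency in eligibility that should be fixed; it is not a fatal flaw.

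**What to change.** Reconcile the passages, in one of two ways:

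- To match the stated aim, reword 2.3.1 to require myocardial necrosis in the CTO territory on the baseline CMR, with or without a previous MI, and add the mirror item to 2.3.2.
- If the sponsor does intend prior MI as a separate route, change the Abstract (methods and conclusion), Discussion and Conclusions so that they describe the wider population.

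Under the first option, keep any patients already randomized on history alone in the full analysis set. Pre-specify an analysis restricted to patients with CTO-territory necrosis on baseline CMR. Because that scan precedes treatment, the restriction keeps the randomized comparison, provided the scan is read before allocation or blind to it. Section 2.1 says only that it comes before intervention, while section 4 says before randomization, so state the timing in the same amendment.

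The cost is small: the scan is already planned for every patient, and the price is a short amendment and a few more screen failures.

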#### Exclusion criteria

2.3.2

Patients will be excluded if they have suffered from acute myocardial infarction within the previous 3 months; a lesion located in the left main artery (stenosis ≥50%); rheumatic valvular disease; severe arrhythmia; a history of revascularization within the non-CTO artery; multiple vessels with CTO (more than one CTO artery); lesions unsuitable for PCI; severely abnormal hematopoietic systems, such as platelet counts <100 × 10^9^/L or > 700 × 10^9^/L and white blood cell counts < 3 × 10^9^/L; with active bleeding or bleeding tendencies (active ulcers, short-term ischemic stroke, history of hemorrhagic stroke, intracranial space occupying lesions, recent craniocerebral trauma, and other bleeding or bleeding tendency); severe coexisting conditions, including severe renal function dysfunction [Glomerular filtration rate less than 60 ml/min • 1.73 m^2^), severe hepatic dysfunction [glutamic-pyruvic transaminase (ALT) or glutamic-oxal acetic transaminase (ALT) elevated more than three times that of the upper limit of the normal reference], severe heart failure (NYHA classification III–IV), acute infectious diseases and immune disorders; tumors; surgery within 3 months; a life expectancy less than 12 months; pregnancy or planning to become pregnant; history of allergy or adverse reactions to aspirin, clopidogrel, ticagrelor, stains, contrast material, anticoagulant, or stents. Patients will also be excluded if they cannot tolerate dual antiplatelet treatment; are unable to communicate due to cognitive impairment, auditory, or visual impairment; are participating in another trial for medication or an apparatus and in which the main endpoint has not been reached, or plan to participate in a clinical trial within 12 months of the intervention.

### Intervention

2.4

#### PCI procedure

2.4.1

Experienced operators have been designated to ensure that the success rate of CTO-PCI is above 80%. Procedural success is defined as resulting in residual stenosis of <10% with thrombolysis in myocardial infarction grade 3 flow, in the absence of dissection and thrombosis. The use of a DES and specialized devices will be left to the discretion of the operator.

#### Medication

2.4.2

Patients included in both CTO-PCI group and non-CTO PCI group will be administered aspirin (300 mg) and one P2Y12 receptor antagonist (300–600 mg clopidogrel or 180 mg ticagrelor) before PCI unless they have been treated with these antiplatelet agents previously. Calcium antagonists, nitrates, sodium nitroprusside, and GP IIb/IIIa receptor antagonists will be prepared and administered in any case in which no-reflow occurs in the PCI procedure. After PCI, all patients will be routinely administered one P2Y12 receptor antagonist (clopidogrel 75 mg/d or ticagrelor 90 mg twice daily), aspirin (100 mg/d) and statin once daily for 12 months. Other medications such as beta-blockers, calcium antagonists, and nitrates will be administered according to the clinical status of each patient, considering factors such as heart rate, blood pressure, and cardiac function.

### Evaluation

2.5

#### CMR scanning

2.5.1

CMR will be performed using a Siemens 3.0T whole-body MR scanner (MAGNETOM Verio, A Tim System; Siemens Healthineers, Erlangen, Germany). A 32-element matrix coil will be utilized for data collection, and electrocardiographic gating will be utilized to acquire all sequences. First, the morphologic data from the heart will be acquired with the short-axis plane (from the base to the apex) and long-axis plane of the left ventricle (LV). Next, 0.05 mmol/kg Magnevist contrast agent will be injected intravenously with a high-pressure syringe at 5 mL/s. The first-pass perfusion image (8-mm sections with no intersection gap) will be acquired when magnevist is injected. LGE imaging (8-mm sections with no intersection gap) will be acquired 10 minutes after the intravenous administration of gadolinium (Magnevist, Bayer Healthcare, 0.1 mmol/kg) using a 2-dimensional, phase-sensitive, inversion-recovery, breath-hold sequence.

CMR will be utilized to assess myocardial infarct size, left ventricular mass, LVEF, LVEDV, left ventricular end-systolic volume (LVESV), cardiac output, stroke volume, segmental wall thickening, and myocardial viability in the territory supplied by the artery with CTO.

#### Transthoracic echocardiography

2.5.2

Transthoracic echocardiography (Philips ie33 GE vivid 7) will be utilized to determine left ventricular end diastolic diameter, left ventricular end systolic diameter, LVEF, and segmental wall thickening.

### Experimental endpoints and procedural follow-up

2.6

Patients will be followed-up via outpatient consultation 1, 6, and 12 months following PCI. A follow-up appointment 12-months post-PCI will be conducted at the hospital. Basic characteristics including gender, BMI, waist circumference, comorbidities, medication history, blood pressure, and heart rhythm both at baseline and 1-year post-PCI will be documented by an independent physician. Blood tests assessing routine blood counts, liver and kidney function, blood lipid profiles, fasting blood glucose, glycosylated hemoglobin, hsCRP, and BNP will be recorded at baseline (before angiography) and at 1-year post-PCI. CK, CK-MB, and cTNI levels will be collected at baseline, one day after intervention, one week after intervention, and at 1-year post-PCI.

#### Primary endpoint

2.6.1

The primary endpoint of this SOS-moral study will be difference in cardiac function observed between baseline and 1-year post-intervention, which will be determined by CMR and transthoracic echocardiography.

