### Study design and randomization

2.1

This SOS-moral study is a randomized controlled trial with a multi-center design. The protocol was approved by the ethics committee of Beijing Anzhen Hospital (approval no. 2017059X) and has been registered at ClinicalTrials.gov (identifier: NCT 03372785).

Patients meeting the inclusion criteria will be categorized into two groups at a ratio of 1:1 according to a randomized digital table used to randomly assign patients to the CTO-PCI group (PCI of both the non-CTO artery and a concurrent CTO artery), or the non-CTO PCI group (PCI of only the non-CTO artery). The randomized digital form and interactive voice response mode will be applied to facilitate the randomization procedure. The randomization sequence will be produced and managed by an independent staff member. Before intervention, myocardial viability and cardiac function of patients will be evaluated using CMR. Cardiac function will be assessed using transthoracic echocardiography and CMR. The Seattle angina questionnaire (SAQ), Patient Health Questionnaire 9 and Generalized Anxiety Disorder Scale-7 will be used to evaluate patient QOL. Cardiac function, QQL, and MACE will be observed within 12 months of follow-up. A flow chart outlining the study design is depicted in Figure 1.

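### The primary endpoint rests on CMR alone in the Abstract but on CMR and echocardiography in section 2.6.1, and neither statement names the variable that decides the trial

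*Protocol article*

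**What the plan says.** The Abstract (Methods and results) states: "The primary outcome will be the change in cardiac function evaluated via CMR at a 12-month of follow-up appointment". Section 2.6.1, the formal definition, takes the difference in cardiac function between baseline and one year, "which will be determined by CMR and transthoracic echocardiography".

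Other sections divide the same way. Section 2.1 names both methods: "Cardiac function will be assessed using transthoracic echocardiography and CMR". The Discussion, arguing for the choice of imaging, names one: "CMR will be used to evaluate both the amount of viable myocardial tissue and level of cardiac functioning".

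Neither endpoint statement says which measure of cardiac function is meant. Section 2.7 comes closest: "LVEF has been taken into consideration for the calculation of sample size". It gives no imaging method for that LVEF. Section 2.5.1 lists among the CMR measures "LVEF, LVEDV, left ventricular end-systolic volume (LVESV), cardiac output, stroke volume, segmental wall thickening". Section 2.5.2 says echocardiography "will be utilized to determine left ventricular end diastolic diameter, left ventricular end systolic diameter, LVEF, and segmental wall thickening". LVEF is on both lists.

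Section 2.8 sets one general two-sided threshold of 0.05. The article does not rank the two methods or declare them co-primary.

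**The concern.** A primary endpoint should identify one result that decides whether the trial succeeded. Here two current statements of it disagree on the measuring instrument, and the variable must be inferred from the sample size section. The trial will hold 12-month LVEF from both CMR and echocardiography. If the two give different answers, the article does not say which is the trial's answer, so the choice could be made after the data are seen.

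Two things are at stake: the false-positive rate if either result may be claimed as primary, and the meaning of the stated 90% power if both are required.

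**Working it through.** **Inputs.** From section 2.7: LVEF standard deviation 9, boundary value 4, one-sided alpha 0.025, power 0.90, 216 cases, 10% loss, 240 randomized. From section 2.1: 1:1 allocation. From section 2.8: two-sided 0.05. The article gives no correlation between the CMR and echocardiographic results, so a range is assumed. The same effect and standard deviation are also assumed for both methods.

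**Reproducing the plan's figure.** For one comparison of two means, n per arm = 2(z₀.₉₇₅ + z₀.₉₀)² × SD² / δ². With δ = 4 this is 2 × (1.960 + 1.282)² × 81/16 ≈ 106.4, so 107 per arm. The t-test version gives 107.4, so 108 per arm, or 216 in total, and 216/0.90 = 240. The stated size is therefore that of a single LVEF test with 4 points as the whole difference. (How the 6.5-point difference and the figure of 226 in section 2.7 fit in is a separate matter.)

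At 108 per arm the expected test statistic is 4 / (9 × √(2/108)) = 3.266. The power is Φ(3.266 − 1.960) = 0.904.

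**Two LVEF results, one from each method.** The formulas are:

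- Either counts, two-sided: 1 − P(|Z₁| < 1.96 and |Z₂| < 1.96). If independent, 1 − 0.95² = 0.0975.
- Either counts, false wins for CTO-PCI only: 1 − P(Z₁ < 1.96 and Z₂ < 1.96). If independent, 1 − 0.975² = 0.0494, against a nominal 0.025.
- Both must succeed: P(Z₁ > 1.96 and Z₂ > 1.96), each with mean 3.266.
- One significant and the other not, under the true 4-point effect: 2 × (0.904 − joint power).

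| Assumed correlation | Either counts, two-sided error | Either counts, false win for CTO-PCI | Both required, joint power | Results disagree |
|---|---|---|---|---|
| 0 | 9.75% | 4.9% | 0.818 | 17% |
| 0.5 | 9.1% | 4.5% | 0.839 | 13% |
| 0.8 | 7.8% | 3.9% | 0.862 | 8% |
| 0.9 | 7.0% | 3.5% | 0.874 | 6% |

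With the nominal power of exactly 0.90, the independent case for joint power is 0.90 × 0.90 = 0.81, which gives the lower end of the 0.81 to 0.87 range.

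**What the plan's size would have to become.** If either method may win and alpha is split equally (one-sided 0.0125 each), power per test at 216 is 0.847. Restoring 0.90 per test needs 254 evaluable, and 254/0.90 rounds up to 283 randomized. With one variable by one method, 216 evaluable and 240 randomized stand unchanged at two-sided 5%.

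**The case against.** The strongest reply is that the intended endpoint can be inferred. Section 2.7 links the trial's purpose, an effect on cardiac function, to LVEF, the only variable used for sizing. The Abstract and the Discussion favour CMR. The lists in sections 2.5.1 and 2.5.2 describe what each scan yields and are not endpoint lists. This is fair as far as the variable goes. A reader might infer that any volume, diameter or wall-thickening measure could be claimed as primary, but the article does not support that. The method remains open, because sections 2.1 and 2.6.1 name both.

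A reader might also infer that type I error is not held at 5%. No section says that success on either method is enough. The wording of section 2.6.1 could equally mean that both must succeed, in which case alpha is not inflated and power is lost instead. Nor can the article's silence on multiplicity, or on what follows if the results disagree, count as a fault in itself: a condensed article may leave such rules to an analysis plan that is not shown. This also stands.

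The 9.75% figure assumes independence, which is implausible for two measurements of the same quantity in the same patients. It is an upper limit for two tests.

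None of this removes the conflict between the Abstract and section 2.6.1. A later plan could add a rule, but the two published definitions would still differ.

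**Conclusion.** The point holds as an inconsistency in the definition of the primary endpoint. The Abstract and section 2.6.1 disagree on method, neither names the variable, and the sizing LVEF in section 2.7 has no stated method. On the most favourable reading, that LVEF is meant, two candidate primary results remain.

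The size of the consequence depends on a rule the article does not state. If either result counts at two-sided 0.05, the error is about 7.0% to 9.75%, or 3.5% to 4.9% against 2.5% for false wins favouring CTO-PCI. If both must succeed, alpha holds and joint power is about 0.81 to 0.87. These figures rest on assumed correlations of 0.9 down to 0 and on equal effect and variability for the two methods. Under neither rule does the stated combination of alpha and 90% power describe the test.

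Because the primary endpoint decides the trial's conclusion, this should be corrected.

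**What to change.** In section 2.6.1 and the Abstract, state one primary endpoint: the between-group difference in change in LVEF from baseline to 12 months, measured by CMR. This agrees with the Abstract's method, the sizing variable in section 2.7 and the Discussion's case for CMR. Make echocardiographic LVEF and all other CMR and echocardiographic measures secondary or supportive, and align section 2.1. In section 2.7, state which method the LVEF difference and standard deviation refer to.

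If the sponsor prefers to keep both methods as primary, the article must say whether either or both must succeed and restate alpha, power and sample size accordingly.

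The cost of the single endpoint is a dated protocol amendment, with the registry entry brought into line, made before outcome data are seen; section 2.3 has enrolment starting in April 2018. Echocardiographic results lose primary status. No patients or measurements are added.
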